**Figure 1 figure1:**
[figure not shown]
Flow diagram depicting the study schedule for the assessment of the effectiveness of composite Ayurveda regimen for the management of rheumatoid arthritis. ADR: Adverse Drug Reaction; DAS: disease activity score; ESR: erythrocyte sedimentation rate; VAS: visual analog scale.

### Intervention

The treatment regime was customized based on the major patterns of disease presentation in each participant. All of them have been given oral medication Ayush-SG one gram in tablet form twice a day with lukewarm water after meals and *Rasnasaptak Kashaya* 20 mL twice a day (80 mL water added in 10 g of course powder and boiled until remains 20 mL) before meals for 12 weeks. Along with this, *Brihat Saindhavadi Taila* has been given for local application in cases with only articular manifestations (joint pain, stiffness, and minimal swelling). Participants with severe pain and swelling (boggy swelling or affusion elicited by fluctuation test), elevated body or joint temperature, and redness of joint, have been administered *Guduchi Ghana vati* (*Sanshamani Vati*) orally in the dose of 500 mg twice a day with lukewarm water after meals and *Dashanga Lepa* for local application. *Punarnavadi Mandura* has been given orally in a dose of 500 mg twice a day with lukewarm water after meals in participants with mild aching, stiffness, fatigue, and anemia.

Incidental medication has been given to the participants in case of any associated complaints. For constipation, *Triphala Churna* has been given in a dose of 5 g orally with lukewarm water at night before sleep. For *Mandagni*, *Vaishwanar Churna* has been administered in a 2.5 g dose orally with lukewarm water twice a day just after food. For the participants having insomnia/anxiety, *Ashwagandha Churna*, 3 g has been given orally twice a day. The duration of incidental medication is decided by the investigator as per the requirement.

The medicines were purchased from Ayurveda manufacturing pharmacies that are certified with good manufacturing practices. Ayush-SG was procured from the Central Ayurveda Research Institute’s Ayurveda Pharmacy, Jhansi, Uttar Pradesh, India. All other medicines administered in the study were procured from the Indian Medicines Pharmaceutical Corporation Limited (Mohan, Almora, Uttarakhand, India).

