**Methods:**

The study is a single-arm (pre-post design), community-based interventional study with a black box design being conducted at 6 study centers. A total of 240 participants aged between 18 and 65 years, diagnosed with RA as per the 2010 American College of Rheumatology and the European League Against Rheumatism criteria are recruited as per the selection criteria. All the participants received Ayush-SG and *Rasnasaptak Kashaya* for 84 days along with customized treatment as per the disease presentation and associated complaints. The outcome measures include the change in disease activity score (DAS)-28 with erythrocyte sedimentation rate, disease-specific biochemical and inflammatory markers, Disability Index score, change in the participant’s assessment of pain and frequency of use of conventional analgesics or nonsteroidal anti-inflammatory drugs from baseline. The tolerability of interventions is assessed through the occurrence of adverse events. Categorical variables will be analyzed with McNemar chi-square test, and continuous variables will be assessed using the paired *t* test or Wilcoxon test for pre-post assessment. The level of significance will be 5%.

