### Exclusion Criteria

Participants presenting with complications of RA, for example, deformity of joints/bones, pleura-pericardial disease, participants with extra-articular manifestations of RA and gastrointestinal symptoms, those with joint prosthesis or unable to walk without support or confined to a wheelchair, participants with Hemoglobin <8 g/dL, diagnosed with other arthritis like osteoarthritis, gouty arthritis, tuberculous arthritis, psoriatic arthritis, spondyloarthropathy, active fibromyalgia, juvenile chronic arthritis, ulcerative colitis, or other systemic inflammatory conditions and autoimmune diseases, having blood pressure ≥ 160/100 mm Hg, or hemoglobin A_1c_ (HbA_1c_)>8%, on medication with corticosteroids, antidepressants, anticholinergics, etc or Ayush interventions/folk medicine or any other drugs that may influence the outcome of the study are excluded from the study. Participants with diagnosed concurrent neurological, pulmonary, or endocrine disorder, or unstable cardiovascular disease, with concurrent serious hepatic disorder (defined as aspartate aminotransferase or alanine aminotransferase, total bilirubin, alkaline phosphatase > 2 times upper normal limit) or renal disorders (defined as S Creatinine > upper normal limit); participants with alcohol use disorder (CAGE score >2) or any other substance abuse; and pregnant or lactating woman are not enrolled in the study.

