### Concomitant and Rescue Medication

Concomitant therapy has been continued for diabetes mellitus, hypertension, or any other disease, that has not been specifically mentioned in the exclusion criteria**.** The investigators may prescribe any concomitant medications or treatments deemed necessary to provide adequate supportive care during the intervention period**.** The name, indication, dose, unit, frequency, start date, and stop date (if applicable) for all interventions (medicine/procedure/therapy) have been recorded on each participant’s case record form (CRF)**.** Administration of any rescue medicines in case of any medical emergency has been documented in the CRF.

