### Outcome Measures

The primary outcome of the study is the change in the DAS-28 score (with ESR) [18] and it is assessed at baseline and the end of the treatment (84th day). Secondary outcomes include the change in disease-specific biochemical and inflammatory markers (RA factor, C-reactive protein, and ESR) and serum immunoglobulin levels (Immunoglobulin G and Immunoglobulin M), participants’ assessment of Pain, Global assessment of disease activity, change in Disability Index score and frequency of use of conventional analgesic/NSAIDs medicines and occurrence of adverse events if any. The change in disease-specific biochemical and inflammatory markers and serum immunoglobulin levels are assessed at baseline and on the 84th day. The participants’ assessments for pain and global assessment of disease activity are assessed using the visual analog scale [19] ranging from 0 mm (no pain) to 100 mm (worst possible pain) at baseline, 28th day, 56th day, and 84th day. The change in Disability Index score is assessed using the Indian Health Assessment Questionnaire [20] at baseline, 28th day, 56th day, and 84th day. The frequency of use of conventional analgesic/NSAIDs medicines and occurrence of adverse events are also assessed in a time frame of baseline, 28th day, 56th day, and 84th day (Figure 1).

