### Data Collection Methods

Demographic data, clinical history, details of concomitant medications, the score of 2010 American College of Rheumatology and the European League Against Rheumatism criteria, DAS-28, and other assessment parameters of the participants have been recorded in the CRF. The participants were followed up on the 28th day, the 56th day, and the 84th day**.** During follow-ups, the occurrence of any symptom and the need for any rescue medication have been recorded. The contact number of the investigator along with the address of the CCRAS institute have been provided to the participants at the time of enrollment**.** Participants have been instructed to inform about any adverse event that happens during the study period**.**

Besides a hard copy of CRF, the data have been recorded in e-CRF also. All source documentation supporting entries into the CRFs are maintained and will be kept readily available. To ensure the quality, the data are checked for consistency, omissions, and any apparent discrepancies. The reason for withdrawal or dropping out of participation is recorded in the CRF.

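### A complaint that starts or worsens on treatment fits both the incidental-medicine rule and the adverse-event rule, and only the second feeds tolerability, so harm may be undercounted

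*Protocol article*

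**What the plan says.** All references are to the protocol article.

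- **Intervention.** "Incidental medication has been given to the participants in case of any associated complaints". Three kinds of complaint are named: constipation, Mandagni, and insomnia or anxiety. "The duration of incidental medication is decided by the investigator as per the requirement". Nothing is said about when the complaint must have begun, or whether its treatment is also logged as an adverse event.
- **Abstract, Methods.** All participants receive the two core medicines "along with customized treatment as per the disease presentation and associated complaints".
- **Withdrawal Criteria.** For an adverse event of any kind, the ethics committee and the safety board are informed and the participant leaves the study.
- **Tolerability.** It is part of the secondary objective. The abstract states: "The tolerability of interventions is assessed through the occurrence of adverse events". Outcome Measures adds that "occurrence of adverse events are also assessed in a time frame of baseline, 28th day, 56th day, and 84th day". Incidental-medicine use and follow-up symptoms are not listed as outcomes.
- **Data Collection Methods.** "During follow-ups, the occurrence of any symptom and the need for any rescue medication have been recorded". Participants are also told to report adverse events.
- **Concomitant and Rescue Medication.** "The name, indication, dose, unit, frequency, start date, and stop date (if applicable) for all interventions (medicine/procedure/therapy) have been recorded" on the case record form.
- **Exclusion Criteria.** The list includes "participants with extra-articular manifestations of RA and gastrointestinal symptoms".

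**The concern.** The article states two rules for what may be the same event. Take insomnia first noted at day 28. As an associated complaint it gets an incidental medicine and, by implication, the participant carries on. As an adverse event it brings two notifications and withdrawal. The article gives no criterion for choosing between them.

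The choice of label decides whether the event reaches the tolerability result. The complaint label costs a site nothing, whereas the adverse-event label costs reports and a participant. Any pull on the label is therefore towards fewer recorded adverse events.

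The trial has a single arm, so no comparator rate could reveal under-classification, and the absolute event count carries the tolerability conclusion. The regimen combines several oral products, and digestive complaints are among those that the article expects to treat. If such complaints arise on treatment and stay outside the count, the regimen will look better tolerated than the case record forms show.

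**Working it through.** This is a question of classification, so the check sets the rules side by side for each kind of complaint.

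**Step 1. Is there an onset limit?** Intervention covers any associated complaint and sets none. Withdrawal Criteria covers any adverse event and does not exempt complaints that receive incidental medicine.

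| Complaint | Intervention | Withdrawal Criteria | In the tolerability count? |
|---|---|---|---|
| Present at baseline, not worse | Applies | Not obviously engaged | No, and properly so |
| New or worse after first dose | Applies | Can apply | Only if labelled an adverse event |

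The second row is the gap: both rules can apply, and their consequences differ.

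**Step 2. Can on-treatment onset be expected?** Exclusion Criteria can be read in two ways.

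- *Gastrointestinal symptoms exclude on their own.* Constipation or Mandagni should then be absent at entry, and a case treated later under Intervention would be new on treatment.
- *They exclude only together with extra-articular manifestations.* These complaints may then be present at entry, and onset is open.

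Insomnia and anxiety are not named as symptoms in Exclusion Criteria, so onset is open for them on either reading. The overlap in Step 1 exists on both readings. The first only makes it more likely to arise for digestive complaints.

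**Step 3. Do other records close the gap?** Follow-up symptoms are recorded, and so are the indication and start date of every medicine. Neither passage says that these records are turned into adverse events, and neither says that they are not. The information to classify is collected, but the article does not state how it is classified. The laboratory tests at baseline and day 84 would not detect constipation or insomnia.

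**Step 4. Can the size be computed?** It would need two quantities: *p*, the share of participants with a new or worsened complaint, and *f*, the share of those logged only as a complaint. Then

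recorded participants = 240 × *p* × (1 − *f*).

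The article gives neither *p* nor *f*. As pure assumption:

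| *p* | *f* = 0 | *f* = 0.5 | *f* = 1 |
|---|---|---|---|
| 5% | 12 | 6 | 0 |
| 10% | 24 | 12 | 0 |
| 20% | 48 | 24 | 0 |

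At each *p* the loss runs from none to all. The table shows that the size is undetermined. It does not estimate it.

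**The case against.** The strongest reply is that associated complaints are presenting features. The abstract pairs them with disease presentation as a basis for customised treatment, and the Introduction names Mandagni as a cause of Amavata, the condition to which the article likens rheumatoid arthritis. Many of these complaints were plausibly there at entry and are not harms. That stands for many cases, but the text does not confine incidental medicine to them.

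A second reply is that capture is adequate. Adverse events are assessed at every visit, symptoms are recorded at follow-up, and participants are told to report events. Asking about any symptom is an ordinary way to find adverse events. This also stands, as far as recording goes. It does not say which label a treated complaint receives.

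A third is that a detailed adverse-event definition belongs in the full protocol or analysis plan. That is right, and its absence from an article is no finding. The point here is that two stated rules overlap with different consequences.

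A reader might go further in two ways that the documents do not support.

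- **That new symptoms are handled as complaints instead of as adverse events, so harm is undercounted.** No passage keeps treated complaints out of the adverse-event records. Undercounting is possible but not shown.
- **That the 18 non-completers (240 − 222) cap the number of participants with a recorded adverse event.** Adverse events are also assessed on day 84, when a participant may already count as a completer. Withdrawal has other causes too, such as unwillingness or worsening disease, so 18 is not a count of adverse events either. Adding assumed complaint rates to it gives no usable figure.

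**Conclusion.** The point holds as an ambiguity with a predictable direction. A complaint that starts or worsens on treatment fits both the incidental-medicine rule and the adverse-event rule, and only the adverse-event label feeds tolerability. Treatment-emergent complaints can therefore be left out and harm may be undercounted. Whether this happened, and how often, cannot be computed from the documents.

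The conclusion assumes only that the two rules mean what they say and that at least some treated complaints began or worsened after the first dose. It does not depend on how the gastrointestinal exclusion is read. It concerns a secondary objective and leaves the primary outcome untouched. It is worth correcting because the trial has no comparator, the data are already collected, and the article reports the analysis as still in progress.

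**What to change.** **In the tolerability analysis:**

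1. From the follow-up symptom records and the indication and start date of each medicine, classify every complaint and every incidental-medicine start as present at baseline, or as new or worsened after the first dose.
2. Report new or worsened complaints, other than rheumatoid arthritis symptoms, as treatment-emergent events beside the investigator-labelled adverse events. Count an event that appears in both sources once.
3. Leave out rheumatoid arthritis symptoms already measured as efficacy outcomes. Also leave out complaints present at baseline that did not worsen, even if first treated later. A start date after the first dose is not enough by itself to make an event.

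**In the protocol text:** the sponsor must reconcile Exclusion Criteria, Intervention and Withdrawal Criteria on how the same complaint is handled. No clinical rule is proposed here.

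**Cost:** one extra derivation from data that the article says are on the case record form, with no new visits or measurements. The reported event rate may rise.

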### Withdrawal Criteria

The participant has been withdrawn from the study if they have not been willing to continue, if there has been a worsening of RA symptoms, or if they have developed any other illness mentioned in the exclusion criteria. The decision to withdraw a participant from the study has been made solely by the Investigator, who has then had to provide a detailed justification and indicate the line of further management if needed.

In the case of any adverse event, serious adverse event, or adverse drug reaction, the Institutional Ethics Committee (IEC) and Data Safety Monitoring Board are to be informed and participants are to be withdrawn from the study.

### Compliance

During the intervention period, compliance has been evaluated based on the amount of study medication that is consumed. This has been assessed using a compliance assessment form issued to the participants to fill up.

### Concomitant and Rescue Medication

Concomitant therapy has been continued for diabetes mellitus, hypertension, or any other disease, that has not been specifically mentioned in the exclusion criteria**.** The investigators may prescribe any concomitant medications or treatments deemed necessary to provide adequate supportive care during the intervention period**.** The name, indication, dose, unit, frequency, start date, and stop date (if applicable) for all interventions (medicine/procedure/therapy) have been recorded on each participant’s case record form (CRF)**.** Administration of any rescue medicines in case of any medical emergency has been documented in the CRF.

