## Introduction

### Background

Rheumatoid arthritis (RA) is a chronic inflammatory autoimmune disease that can damage joints and affect extra-articular organs. In 2019, 18 million people worldwide were living with RA. Women accounted for 70% of cases, and over half were older than 55 years [1]. The articular manifestation of RA includes symptoms such as musculoskeletal pain, swelling, and stiffness of joints. It is usually symmetric and initially manifests in small joints and progresses to larger joints. Over time, joint inflammation can lead to joint destruction, including loss of cartilage and bone erosion [2]. The symptoms of RA vary in patients; some patients have mild self-limited disease, while many experience joint destruction, severe physical disability, and multiple comorbidities. RA tends to be progressive in nature, involving a worsening of symptoms over time, and often begins for many people during the early or middle years of life, thus causing a heavy burden on society in terms of disability, health, and economic costs. The available evidence for pain management in RA involves the use of disease-modifying antirheumatic drugs and medications such as nonsteroidal anti-inflammatory drugs (NSAIDs) which play an important role in its management but may suppress the immune system and, lead to an increased risk of infections as well other side effects as gastrointestinal disturbances [3,4]. People from all over the world are also developing an interest in traditional herbal practices. It is reported that 60% to 90% of persons with arthritic conditions use complementary and alternative medicines [5-7]. In a study conducted in the United States, it was reported that around 60% of persons with arthritic conditions including RA use complementary and alternative medicines. Of these, 28% reported a history of herbal therapies, and 22% used diet supplements [8].

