### Statistical Analysis

After data collection, verification of its accuracy and limits will be done. The filtered data will be used for additional analysis and interpretation. The Categorical variables will be reported in number (percentage) and analysis of pre-post-trial outcomes will be done by the Mc-Nemar chi-square test. The continuous variables (like scores and lab parameters) will be analyzed by paired *t* test/Wilcoxon test as per the distribution of data in the pre-post trial situation. The assessment parameters assigned in more than 2 follow-ups will be analyzed using the r-ANOVA/Friedman test/ Cochran Q test. The continuous data having normal distribution will be represented as mean (SD) and the data not having normal distribution as median (IQR). The 5% level of significance will be used throughout the analysis. The SPSS (version 26.0; IBM Corp) software will be used to conduct the analysis.

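### Conventional drugs started, increased or stopped on study can remain in the uncontrolled DAS-28 comparison and be attributed to the regimen

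*Protocol article*

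**What the plan says.** The study is single-arm and pre-post. The primary outcome is the change in DAS-28 (with ESR) from baseline to day 84.

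- **Drugs at entry.** The Exclusion Criteria bar people "on medication with corticosteroids, antidepressants, anticholinergics, etc or Ayush interventions/folk medicine or any other drugs that may influence the outcome". This governs enrolment.
- **Drugs during treatment.** Under Concomitant and Rescue Medication, treatment for diseases not named in the exclusion criteria continues, and then: "The investigators may prescribe any concomitant medications or treatments deemed necessary to provide adequate supportive care during the intervention period". Each drug's name, indication, dose and dates go in the case record form (CRF).
- **Withdrawal.** The triggers are unwillingness, worsening RA symptoms, an adverse event, or "if they have developed any other illness mentioned in the exclusion criteria". The last refers to an illness, not to a drug.
- **Analysis.** The Statistical Analysis section compares continuous outcomes by a paired t "test/Wilcoxon test as per the distribution of data in the pre-post trial situation", with no term for other drugs.
- **Analgesic use as an outcome.** The abstract lists change in "frequency of use of conventional analgesics or nonsteroidal anti-inflammatory drugs from baseline". Outcome Measures has it recorded at baseline and days 28, 56 and 84: "The frequency of use of conventional analgesic/NSAIDs medicines and occurrence of adverse events are also assessed in a time frame of baseline".
- **Role of conventional drugs.** The Background says of DMARDs and NSAIDs: "which play an important role in its management".

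**The concern.** A randomised trial can compare concomitant drug use between arms. Here there is no second arm, so the DAS-28 change is the regimen's effect plus everything else that altered over 84 days. Conventional RA drugs are one such source, and the article itself regards them as important in treating the disease.

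The entry rule recognises this by keeping out users of drugs that could influence the outcome. The on-study rules do not carry that protection forward: a drug that would have barred someone at screening can be prescribed later without ending participation. Starting or increasing such a drug would flatter the regimen. Stopping or reducing one would work against it, which is possible only for drugs whose users could enroll. What is at stake is the interpretation of the primary result, and with it the article's conclusion that this design is a more reliable way to evaluate effectiveness.

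**Working it through.** **Step 1: can a drug change stay in the primary comparison?**

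| Event on study | Ends participation under Withdrawal Criteria? |
|---|---|
| RA worsens and treatment is escalated | Yes (worsening RA) |
| Drug given for an adverse event | Yes (adverse event) |
| New illness named in the exclusion criteria | Yes |
| NSAID/analgesic for persistent but not worsening pain | No |
| Corticosteroid or DMARD started or increased with none of the above triggers | No |
| NSAID/analgesic or DMARD reduced or stopped | No |

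The last three rows are the gap. The supportive-care condition narrows it, but it lists no class and leaves the judgement to the investigator; pain relief in RA fits within it.

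**Step 2: how large could the effect be?** The documents give no SD, no expected effect and no drug-use rate, and the sample size rests on feasibility, so there is no planned figure to reproduce. From the documents: 222 completers and a 5% level. Assumed: a two-sided test; SD of change 1.2 (range 1.0 to 1.5); a net share f of 10% to 30% who start or increase an RA-active drug; a gain e of 0.3 to 0.6 DAS-28 units each.

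Precision: SE = 1.2/√222 = 0.0805; 95% half-width = 1.971 × 0.0805 = 0.159 (0.132 at SD 1.0, 0.198 at SD 1.5).

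Shift in the mean = f × e. The chance of a significant improvement when the regimen does nothing comes from the noncentral t distribution with 221 degrees of freedom and noncentrality shift/SE:

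| f | e | Shift | SD 1.2 | SD 1.0 | SD 1.5 |
|---|---|---|---|---|---|
| 0 | – | 0 | 2.5% | 2.5% | 2.5% |
| 10% | 0.3 | 0.03 | 5.6% | 6.5% | 4.8% |
| 10% | 0.6 | 0.06 | 11.2% | 14.2% | 8.6% |
| 30% | 0.3 | 0.09 | 19.8% | 26.6% | 14.2% |
| 30% | 0.6 | 0.18 | 60.5% | 76.1% | 42.9% |

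Share at which the shift equals the half-width (SD 1.2): 0.159/0.6 = 26%; 0.159/0.3 = 53%. Net stopping by the same shares would give equal shifts in the other direction, if users were eligible.

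**Step 3: precision of a no-change group.** If 10% to 30% changed a drug, 222 × 0.90 ≈ 200 to 222 × 0.70 ≈ 155 remain. Half-widths at SD 1.2 are 1.972 × 1.2/√200 = 0.167 and 1.975 × 1.2/√155 = 0.190.

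**The case against.** The strongest reply has four parts.

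1. *Prescribing is limited and withdrawal closes most of the route.* A reader might infer that any drug may be given without restriction. The text does not say that: prescribing must be necessary for supportive care, and a flare or adverse event, the main reasons to escalate, ends participation. This stands, and it makes the upper end of the assumed range less likely. It does not reach the last three rows of the first table.
2. *This is a condensed article with no SAP shown.* A prohibited-drug list or an adjusted analysis may exist elsewhere. This stands to the extent that the absence of adjustment is not in itself the finding. The finding is what the article does fix: an open on-study rule, with no matching withdrawal trigger, in an uncontrolled design.
3. *Drug use is visible.* NSAID/analgesic frequency is a secondary outcome and all drugs are recorded. True, but recording alone does not separate their effect from the regimen's; it makes the remedy cheap.
4. *The size is assumed.* Also true. A reader might infer that the DAS-28 result is inflated. The documents show neither that such drugs were used nor in which direction use changed.

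A reader might also infer that the exclusion contradicts the NSAID outcome, so that baseline use must be zero and the outcome could only worsen. The documents do not support this firmly. NSAIDs are not named among the excluded drugs, and measuring change in their use from baseline makes most sense if users could enter. The catch-all wording leaves the matter open, so it calls for clarification and no more.

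**Conclusion.** The concern holds in a limited form. As written, a corticosteroid, DMARD or NSAID/analgesic that is started, increased or stopped without worsening RA or an adverse event remains in the single-arm DAS-28 comparison, and its effect would be attributed to the regimen. The direction and size cannot be determined from the article. Under the assumptions shown, the shift is 0.03 to 0.18 units: minor at low shares, and larger than the confidence half-width only above about 26% net starters at 0.6 units each. That is enough to justify a supportive analysis while analysis is still under way, but not to say that the primary result is wrong.

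**What to change.** Before the analysis is final, specify two analyses from the CRF drug records:

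- **Supportive DAS-28 analysis.** Participants who started or increased a corticosteroid, DMARD or NSAID/analgesic are given no improvement: zero change if their DAS-28 improved, their observed change if it worsened. Scoring all of them as zero would be wrong, because it would improve the value of anyone who worsened. Fix the minimum duration of use that counts in advance, without sight of outcomes.
- **Descriptive DAS-28 change** in participants with no change in these drugs, which also sets aside those who stopped or reduced one.

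Report both beside the as-measured result, and qualify the effectiveness conclusion if they differ. As a clarification, state whether NSAID/analgesic and DMARD users were eligible, and report NSAID/analgesic use at each visit with baseline users and new users shown separately.

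The cost is a little extra analysis; no new data are needed. The supportive estimate may be smaller. The no-change group is selected after baseline, so it can only be descriptive, and it is less precise (half-width 0.17 to 0.19 against 0.16 under the assumptions above). Follow-up is complete, so the prescribing rule itself can no longer be changed.
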